### Trial analyses

A full statistical analysis plan will be written prior to completion of data collection and analyses. The null hypothesis is that there will be no significant difference in the primary and secondary outcomes between intervention and control arms at (a) 12 months, and (b) 2 years. The first 12 months will be a standard comparison of the intervention against control (hypothesis a), while the assessment at 2 years will be a comparison between immediate versus delayed treatment (hypothesis b). We will also have a 2 years’ follow-up and be able to look at the longer term effects of the intervention in patients receiving it immediately.

The distribution of GEPs will be examined and, based on the prior work by Leocani and colleagues [3], it is likely that this will be relatively normally distributed or slightly skewed. In this case we will use conventional linear regression models to estimate the differences in mean GEP between study arms, with 95 % confidence intervals and *P*-values, to address the above hypotheses (a) and (b) in turn, adjusting for covariates, including baseline GEP and disease type. These primary analyses will follow the intention-to-treat principle.

In addition, a secondary analysis of the measures of GEP at 0, 6, 12, 18 and 24 months will investigate the effect of the intervention over time. This investigation is likely to use a random effects analysis, to allow for individual variation in the level of and degree of change in GEP. Our pre-specified sub-group analyses will compare the magnitude of the treatment effect on GEP between sub-groups defined by gender, baseline GEP and disease type.

Analysis of secondary outcomes will be clearly delineated from the primary analysis in any statistical reports produced. Secondary outcomes (MSFC, category rating scales, annual overall patient and treating physician assessments of efficacy) will be scored according to standard methodology and analysed in a similar way to the primary outcome. Conventional linear regression models will be used for continuous secondary outcome measures, and logistic regression or related methods for binary and categorical outcome measures.

Imaging results will be analysed using a multi-level model enabling accommodation of missing data. The incidence rates of AEs and SAEs will be summarised by treatment group. The proportion of participants discontinuing treatment will be summarised by reason and by treatment group.

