### Sample size estimation

We will randomly allocate 40 patients, 30 with secondary progressive disease (SPMS) and 10 with primary progressive disease (PPMS), to each arm of the study, allowing a difference of between 0.63 and 0.73 of a standardised difference in GEP between the arms to be detected with 80 % power at the 5 % significance level, assuming a loss to follow-up rate of between 0 and 25 % respectively. Our experience suggests that, given the close involvement of patients and staff, we will achieve around 95 % follow-up.

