## Discussion

Our phase I study established the feasibility of autologous bone marrow infusion in patients with MS, provided good evidence of safety and offered preliminary suggestions of efficacy [1]. ACTiMuS will determine whether infusion of autologous marrow does indeed lead to improvements in CNS conduction in patients with progressive MS.

Our proposed trial utilises a randomised, blinded, immediate-versus-delayed therapy controlled protocol. There are two reasons for this design. Firstly, to maintain blinding all patients must believe they could be receiving active intervention, and so all must undergo marrow harvesting. It then becomes unreasonable (and arguably unacceptable) for participants not to receive therapy. This tension is resolved by treating all subjects, but establishing a control arm by comparing immediate versus delayed administration using the stepped wedge design. Secondly, there is very limited evidence as to whether any benefit associated with BM stem cells remains constant, declines or even improves over time. By comparing immediate with delayed therapy we can test whether an additional year of follow-up is associated with any differences in outcomes.

The difficulties of demonstrating neuroprotective or reparative effects over relative short periods of time in progressive MS have been well documented [21]. The GEP has been developed as a tool that, by combining multimodal evoked potential recordings to a single score, may be used to monitor the evolution of MS in individual patients. It has also been employed as a surrogate endpoint in clinical trials, and longitudinal studies in significant numbers of patients with MS (>80) have validated the GEP as a marker of the severity of CNS damage and its progression [3, 22]. Our phase I study helped support the view that electrophysiological assessment represents a sensitive and objective surrogate approach to exploring possible improvement in patients with chronic disability in MS [1] and, combined with the supportive evidence outlined above, justifies our inclusion of change in GEP as the primary outcome measure.

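### Two GEP comparisons, at 12 months and at 2 years, are both called primary without ranking, and the single power statement is not tied to either

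*Protocol article*

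**What the plan says.** Four places in the protocol article bear on this.

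- **Trial analyses, the null.** It covers "no significant difference in the primary and secondary outcomes between intervention and control arms at (a) 12 months, and (b) 2 years". The next sentence describes (a) as intervention against control over the first year and (b) as immediate against delayed treatment.
- **Trial analyses, the method.** Linear regression will estimate differences in mean GEP "with 95 % confidence intervals and *P*-values". The models are meant "to address the above hypotheses (a) and (b) in turn, adjusting for covariates, including baseline GEP and disease type. These primary analyses" are to follow intention to treat. The repeated-measures model of GEP over all five visits is labelled secondary. No order of testing and no rule for success is given for (a) and (b).
- **Primary outcome measure.** One outcome is named: the change in GEP over the 12 months that follow marrow infusion.
- **Sample size estimation.** There are 40 patients per arm, "allowing a difference of between 0.63 and 0.73 of a standardised difference in GEP between the arms". The power and level attached to that range are given once, as "to be detected with 80 % power at the 5 % significance level". Neither (a) nor (b) is named, and no time point is given.

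Two further statements matter for (b). Under Bone marrow harvest and infusion, each participant receives at one year whichever product was not given at harvest. The Discussion says "there is very limited evidence as to whether any benefit associated with BM stem cells remains constant, declines or even improves over time".

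**The concern.** A protocol should fix which comparison decides the trial. This one puts two on the primary side of the line and does not rank them, and they answer different questions. Comparison (a) is a test of marrow against placebo. Comparison (b) compares two arms that have both had marrow, one of them a year earlier.

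Two things are at stake. First, if success on either test were allowed to carry the trial, the chance of a false positive claim would exceed 5%. Second, the trial could end with (a) positive and (b) null, or with (a) null and (b) positive, and the article gives no agreed reading of either result. The power statement does not help, because it does not say which contrast it covers. The definition of the primary outcome does not help either, because in the delayed arm its 12-month window after marrow runs from month 12 to month 24.

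**Working it through.** **1. The plan's own figure.** Inputs from Sample size estimation: 40 per arm, loss of 0 to 25% (so 40 to 0.75 × 40 = 30 analysed per arm), 80% power, 5% level. Sidedness is not stated; two-sided is assumed because it reproduces the figures. In SD units, the detectable difference is (1.960 + 0.842) × √(2/n).

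- n = 40: 2.802 × 0.2236 = 0.63 (noncentral t: 0.634)
- n = 30: 2.802 × 0.2582 = 0.72 (noncentral t: 0.736)

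Power by noncentral t is 79.5% for 0.63 SD at 40 per arm and 79.4% for 0.73 SD at 30 per arm. The stated range of 0.63 to 0.73 is reproduced. It is the figure for one two-sided 5% test.

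**2. Error rate if either test could count.** Assume that each test is two-sided 5%. This is inferred from the sample size section and the 95% intervals; the article gives no level per test. Assume also that a positive result on either one supports a claim. Family-wise error = 1 − P(|Z₁| < 1.96 and |Z₂| < 1.96), with Z₁ and Z₂ bivariate normal with correlation ρ. For ρ = 0 this is 1 − 0.95² = 9.75%. Both tests use the same patients, so ρ should be above 0. The documents do not give it, so a range is shown.

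| Assumed ρ | 0 | 0.3 | 0.5 | 0.7 | 0.8 | 0.9 |
|---|---|---|---|---|---|---|
| Family-wise error | 9.75% | 9.5% | 9.1% | 8.35% | 7.8% | 7.0% |

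If (b) is tested only after (a) is significant, or if both must be significant, the rate does not exceed 5%.

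**3. What (b) measures.** Let g(t) be the mean benefit, in SD units, t months after marrow. Assume that it is the same function in both arms, although one arm receives its marrow on the day of harvest and the other receives it thawed a year later. Then:

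- contrast (a) at 12 months = g(12)
- contrast (b) at 24 months = g(24) − g(12)

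For illustration take g(12) = 0.63, 40 analysed per arm, and the same SD at both times.

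| Course of benefit in the second year after marrow | g(24) | Contrast (b) | Chance that (b) is significant |
|---|---|---|---|
| Half lost | 0.315 | −0.315 (favours delayed) | 28.5% |
| Constant | 0.63 | 0 | 5% |
| Grown by half | 0.945 | +0.315 | 28.5% |
| Accrues at a steady rate | 1.26 | +0.63 | 79.5% |

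The same marrow effect at 12 months is therefore compatible with a (b) that is null, reversed or as large as (a). The Discussion says that evidence on which course applies is very limited.

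**4. Comparison of definitions.** The primary outcome window is months 0 to 12 in the immediate arm and months 12 to 24 in the delayed arm. Comparison (a) sets the arms side by side at month 12, when the delayed arm has had only blood. Comparison (b) does so at month 24, two years after marrow in one arm and one year after it in the other. The definition matches neither exactly.

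**The case against.** The best defence is that this is a condensed article which promises a full statistical analysis plan. Testing order and allocation of alpha are commonly set there, so their absence is not in itself a fault. That stands. It does not settle which comparison is primary, because the article does speak to that: it puts both (a) and (b) under the primary label and the repeated-measures model under the secondary one. It then names a single primary outcome elsewhere.

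Four stronger readings are tempting, and the documents support none of them.

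- *The trial's error rate is nearly 10%.* A reader might infer this from two primary P-values. It holds only under an either-test rule for success, which the article neither states nor excludes.
- *The lack of an untreated arm at 2 years inflates type I error.* It does not. If marrow has no effect, (b) compares two randomised arms and is a valid 5% test. The missing arm changes what is estimated and how large it is likely to be.
- *The power calculation is wrong for (b).* The detectable difference for 40 against 40 holds arithmetically at 2 years as well. What lacks support is the expectation of a contrast of that size.
- *A null or reversed (b) is what an effective therapy should give.* That follows only for a one-off benefit that persists or wanes. The objectives also propose neuroprotection, and if marrow slows decline steadily, (b) can be as large as (a). If benefit wanes, a result favouring the delayed arm at 2 years would be a correct finding.

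It is also fair to say that the sentence after the null already describes (b) as immediate against delayed. The reference to a control arm at 2 years is therefore loose wording, which the text itself partly corrects.

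**Conclusion.** The point holds as one of ranking and definition. The article fixes two unranked primary comparisons of GEP beside one primary outcome that matches neither exactly and one power statement that names neither. The effect on error is conditional: about 7% to 9.75% for assumed correlations of 0.9 to 0, if either test alone could support a claim at two-sided 5%, and no more than 5% under a fixed order. Comparison (b) is a legitimate randomised question about timing. However, with 0.63 SD at 12 months its contrast could plausibly lie anywhere from −0.315 to +0.63 SD under the courses shown, so the article gives no basis for expecting 0.63 to 0.73 SD there. These illustrations assume the same effect curve in both arms, equal SDs at both times and no loss to follow-up.

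**What to change.** Five changes of wording in the protocol, carried into the analysis plan:

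1. Trial analyses: name (a), the baseline-adjusted GEP difference at 12 months between immediate marrow and blood, as the single primary test at two-sided 5%.
2. Trial analyses: make (b) a secondary contrast of immediate and delayed treatment. Either report it as a difference with a 95% interval, or test it at 5% only if (a) is significant.
3. Trial analyses: reword the null for (b) so that it does not refer to a control arm at 2 years.
4. Primary outcome measure: redefine the outcome so that it matches (a), that is, GEP at 12 months after the first infusion in both arms.
5. Sample size estimation: state that the 80% power refers to (a), and that the level is two-sided.

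No split of alpha is needed, so the stated power for (a) and the total of 80 patients are unchanged. The cost is that (b) can no longer stand alone as a confirmatory result. Trial status reports recruitment as ongoing, so the change can be made and dated before unblinding.

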#### Secondary analysis of EDSS

The analysis of EDSS will follow the established practice of using time to first progression as the primary endpoint. However, this approach is not optimal in terms of statistical power, and we will be collecting data on disease progression for the full follow-up duration of the trial allowing an analysis based on mean scores over the follow-up period.

#### Exploratory analyses

Exploratory analyses will be clearly delineated from the analysis of primary and secondary outcomes in any statistical reports. The exploratory analysis will include prognostic and predictive factor analysis of disease progression and multivariate analysis of response data.

### Ethical considerations

The ACTiMuS trial will be undertaken in compliance with the World Medical Association Declaration of Helskinki (revised version of Seoul, 2008) and international standards of Good Clinical Practice. Trial design and processes for implementation have the approval of the UK National Research Ethics Committee (NRES Committee South West – Frenchay, 12SW0358).

## Discussion

Our phase I study established the feasibility of autologous bone marrow infusion in patients with MS, provided good evidence of safety and offered preliminary suggestions of efficacy [1]. ACTiMuS will determine whether infusion of autologous marrow does indeed lead to improvements in CNS conduction in patients with progressive MS.

Our proposed trial utilises a randomised, blinded, immediate-versus-delayed therapy controlled protocol. There are two reasons for this design. Firstly, to maintain blinding all patients must believe they could be receiving active intervention, and so all must undergo marrow harvesting. It then becomes unreasonable (and arguably unacceptable) for participants not to receive therapy. This tension is resolved by treating all subjects, but establishing a control arm by comparing immediate versus delayed administration using the stepped wedge design. Secondly, there is very limited evidence as to whether any benefit associated with BM stem cells remains constant, declines or even improves over time. By comparing immediate with delayed therapy we can test whether an additional year of follow-up is associated with any differences in outcomes.

The difficulties of demonstrating neuroprotective or reparative effects over relative short periods of time in progressive MS have been well documented [21]. The GEP has been developed as a tool that, by combining multimodal evoked potential recordings to a single score, may be used to monitor the evolution of MS in individual patients. It has also been employed as a surrogate endpoint in clinical trials, and longitudinal studies in significant numbers of patients with MS (>80) have validated the GEP as a marker of the severity of CNS damage and its progression [3, 22]. Our phase I study helped support the view that electrophysiological assessment represents a sensitive and objective surrogate approach to exploring possible improvement in patients with chronic disability in MS [1] and, combined with the supportive evidence outlined above, justifies our inclusion of change in GEP as the primary outcome measure.

In our phase I trial, we elected to use a filtered preparation of whole bone marrow, rather than one or other selected, growth factor-expanded sub-populations, for several reasons. First, this mimicked the relatively unselected mononuclear cell population that proved beneficial in the first therapeutic studies in rodent demyelinating models [23, 24]. Using unselected BM cells is an increasingly common approach, successfully explored not just in experimental models of stroke [25] and spinal cord injury [26], but also clinically, in patients with myocardial infarction [27, 28], liver disease [29] and peripheral vascular disease [30], and most recently stroke [31].

All BM stem cell sub-populations are in this way included, and several may be beneficial. Multipotent mesenchymal stromal cells (MSCs) are important [32, 33], but CD34-positive haematopoetic stem cells also have reparative potential [34, 35], as do CD133-positive stem cells [36, 37]; other less well-defined sub-populations including Stro-1 positive cells [38–42] may also be valuable [43–45]. Cell selection obviously excludes the majority of cell types; but the available evidence suggests that there is no reason to exclude any specific BM stem cell sub-population; indeed in some circumstances, unfiltered cells have better reparative potential than MSCs [46].

Additionally, the repeated cell cycling and expansion to prepare purified selected MSCs (or other sub-populations) not only induces unwelcome genetic instability [47–49], but may compromise differentiation and repair capacities [50–54]. Finally, if there were benefit from non-selected, non-expanded cells, it would be far easier (and cheaper) to adopt and apply such therapies in relatively non-specialist units, with no requirement for a sterile good manufacturing practice (GMP) cell growth or selection facility.

This ’lumping not splitting’ approach creates the difficulty of obscuring which cell sub-population(s) may actually contribute to the therapeutic effects, but these questions are important opportunities rather than problems: exploring and dissecting the cells and mechanisms relevant to the therapeutic effects should create significant opportunities for developing, refining and improving this form of cell therapy in MS, and we will explore these topics in the laboratory arm of the study which will run concurrently with the clinical trial.

ACTiMuS is the first randomised clinical trial of unfractionated bone marrow-derived cell therapy (without myeloablation) in MS and, as such, represents a landmark in the development of reparative therapies for progressive MS. Furthermore, it will test the sensitivity of employing a modified cross-over protocol with GEP as the primary outcome measure in progressive MS, with potential implication for future clinical trials of reparative and neuroprotective therapies in MS.

## Trial status

Recruitment to the ACTiMuS trial commenced in March 2014 and is ongoing.

## Abbreviations

ACTiMuS: Assessment of Cellular Therapy in progressive Multiple Sclerosis
AE: adverse event
BM: bone marrow
BMCT: bone marrow cell therapy
BSAEP: brainstem auditory evoked potential
CNS: central nervous system
CXR: chest X-ray
DTI: diffusion tensor imaging
EDSS: Expanded Disability Status Scale
FBC: full blood count
FLAIR: fluid attenuated inversion recovery
fMRI: functional MRI
GEP: global evoked potential
GMP: good manufacturing practice
Hb: haemoglobin
MEP: motor evoked potential
MMEP: multimodal evoked potential
MPRAGE: Magnetisation Prepared RApid Gradient Echo
MRI: magnetic resonance imaging
MS: multiple sclerosis
MSFC: Multiple Sclerosis Functional Composite
MSIS-29: Multiple Sclerosis Impact Scale-29
NHSBT: National Health Service Blood and Transplant
OCT: optical coherence tomography
PASAT: Paced Auditory Serial Addition Test
PPMS: primary progressive multiple sclerosis
SAE: serious adverse event
SEP: sensory evoked potential
SPMS: secondary progressive multiple sclerosis
VEP: visual evoked potential
